## 11.1 Sample size calculation

In this trial the aim is to prove non-inferiority of Mini-KIDS compared to LP and SCBT compared to LP. The primary outcome is %SS at 18 months post-randomisation.

The non-inferiority margin was set at 1.0% SS following Bridgeman et al. (2016) and Donaghy et al. (2020). Several studies report a standard deviation on %SS at 18 months varying from 0.4 to 2.1 in different number of children (Arnott et al. 2014; Bridgeman et al. 2016; Donaghy et al. 2020; De Sonnevile-Koedoot et al. 2015). Pooling all these results (weighing them with the number of children per study) we estimated a value of 1.7 for the standard deviation at 18 months on %SS. We adjust the usual one-sided significance level of 2.5% to 1.25% because we are interested in the two comparisons (Mini-KIDS versus LP and SCBT versus LP).

Assuming that in reality there is no difference between the three programs and using a power of 90% and a one-sided significance level of 1.25% we need 73 children in each group to show non-inferiority. Taking into account a 11% dropout (de Sonnevile-Koedoot et al. 2015) we need to randomise 249 children in total (83 children per arm).

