### 11.3.2 Primary outcome analysis

The %SS at 18 months post-randomisation will be determined in two video samples (at home and in the treatment session) and the average will be used.

Considering this is a non-inferiority trial, the primary endpoint is analysed in first instance in the per-protocol population. The per-protocol population are all eligible children who followed the treatment for at least 80%. To establish this, the SLT will carry out a compliance and fidelity checklist for each treatment session (Appendix 9). To correct for the fact that the per-protocol population is a subset of the randomised population we use a weighted linear regression model with %SS at 18 months post-randomisation as outcome and program as predictor and weighting individuals with inverse probability weighting. The weights which are determined in the full dataset of adherers and non-adherers are estimated as an individual's probability to adhere to a certain program given observed confounders like gender, age at assessment, comorbidities, family history of stuttering and recovery of stuttering, parent profile, baseline stuttering severity assessment (%SS and SR), and temperament (CBQ-short version). Post-hoc comparison of SCBT compared to LP and Mini-KIDS to LP using a two-sided 97.5% (correction for two comparisons) confidence interval for the difference in %SS will be compared to the non-inferiority margin.

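### The stated 90% power is not the power of the primary weighted per-protocol analysis, because the sample size allows for 11% dropout only

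*Protocol*

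**What the plan says.** Section 11.1 sets out every input to the sample size:

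- Margin: "The non-inferiority margin was set at 1.0% SS".
- SD: "we estimated a value of 1.7 for the standard deviation at 18 months on %SS".
- True difference: "Assuming that in reality there is no difference between the three programs".
- Level: "We adjust the usual one-sided significance level of 2.5% to 1.25% because we are interested in the two comparisons".
- Result: "using a power of 90% and a one-sided significance level of 1.25% we need 73 children in each group to show non-inferiority".
- Inflation: "Taking into account a 11% dropout", which gives 83 per arm and 249 in total. No other allowance is made.

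Section 11.3.2 then fixes the primary analysis: "the primary endpoint is analysed in first instance in the per-protocol population". That population is the eligible children who followed at least 80% of their treatment, judged from the compliance and fidelity checklists. The model is a linear regression weighted by inverse probability of adherence, with program as the only predictor. Each comparison with LP is read from a two-sided 97.5% confidence interval against the margin.

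Section 8.10.1 keeps every child who stops the trial intervention in follow-up unless the parent withdraws consent.

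**The concern.** The number in 11.1 sizes an analysis in which every child with an 18-month outcome counts once and with equal weight. The analysis that 11.3.2 calls primary discards retained children below the 80% threshold and weights the rest unequally. The first step lowers the number analysed. The second usually lowers the effective number further.

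The protocol clearly foresees non-adherence. It sets 80% thresholds for parent compliance (8.9.1) and therapist fidelity (8.9.2), lists missed sessions, home-practice lapses and therapist drift as possible reasons to stop trial treatment (8.10.1), plans a time-to-switch analysis if switching reaches 10% (11.3.3), and estimates weights from both adherers and non-adherers (11.3.2). Yet none of this enters the sample size.

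What is at stake is how an inconclusive result would be read. Readers are told that a truly equivalent program has a 90% chance of being shown non-inferior in each comparison. If the real chance is nearer 75 to 85%, an interval that crosses 1.0 %SS says less against the program than the protocol suggests.

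**Working it through.** **Inputs from the protocol (11.1):** margin 1.0, SD 1.7, true difference 0, one-sided level 1.25% per comparison, power 90%, dropout 11%, 83 per arm.

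**Assumed, because the protocol gives no figure:** a non-adherent fraction q among retained children of 5 to 30%, and a variance inflation (design effect, DE) from the weights of 1.0 or 1.1. The SD is held at 1.7 in the per-protocol set.

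**Step 1. Reproduce the stated size.** The normal approximation is n = 2 × SD² × (z₀.₉₈₇₅ + z₀.₉₀)² / margin² = 2 × 1.7² × (2.2414 + 1.2816)² / 1.0² = 71.7, so 72 per arm. With the noncentral t distribution, power at 73 per arm is 90.0%, so 73 is the t-based answer. Inflation: 73 / 0.89 = 82.02, rounded up to 83 per arm, and 3 × 83 = 249. All stated figures are reproduced.

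**Step 2. Slack.** Retained per arm: 83 × 0.89 = 73.9 against 73 needed. The slack is about one child per arm (about two by the normal approximation).

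**Step 3. Power of the primary analysis.** Effective number per arm: n = 73.9 × (1 − q) / DE. Power is the probability that a noncentral t variable, with 2n − 2 degrees of freedom and noncentrality 1.0 / (1.7 × √(2/n)), exceeds the one-sided 1.25% critical value.

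| Non-adherent among retained (assumed) | n, DE 1.0 | Power, DE 1.0 | n, DE 1.1 | Power, DE 1.1 |
|---|---|---|---|---|
| 0% | 73.9 | 90.4% | 67.2 | 87.2% |
| 5% | 70.2 | 88.7% | 63.8 | 85.3% |
| 10% | 66.5 | 86.8% | 60.4 | 83.1% |
| 20% | 59.1 | 82.2% | 53.7 | 78.0% |
| 30% | 51.7 | 76.2% | 47.0 | 71.6% |

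**Step 4. Sensitivity to the two assumptions that matter most.**

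- *SD among adherers.* At DE 1.0, 90% power returns if the SD falls to about 1.6, 1.5 or 1.4 at 10, 20 or 30% non-adherence.
- *Overlap of the 11% with non-adherers.* If 20% of all randomised children fall outside the per-protocol set for any reason, 83 × 0.80 = 66.4 remain and power is 86.8%. At 30%, 83 × 0.70 = 58.1 remain and power is 81.4%. Both are before weighting.

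**Step 5. Both comparisons together, for information.** The two comparisons share the LP arm, so with equal arms their correlation is 0.5. At 73 per arm the probability of showing both is about 84% (84.1% by bivariate normal, 83.6% by simulation with pooled variance). With Holm in place of fixed Bonferroni it is about 90% (89.7% by simulation).

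**The case against.** The case against has several parts, and some of it stands.

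- *Nothing is miscalculated.* Correct. The figures 73, 83 and 249 reproduce, and one-sided 1.25% agrees with the two-sided 97.5% interval in 11.3.2. A reader might infer an arithmetic error; there is none. The fault is that the stated power belongs to a different analysis from the primary one.
- *The losses rest on assumed inputs.* Correct, and they are labelled so. At 5% non-adherence without weight inflation the shortfall is small. The SDs cited in 11.1 run from 0.4 to 2.1, so uncertainty in the SD is comparable in size with the loss. A smaller SD among adherers would offset part of it and a larger one would add to it. The protocol argues neither.
- *The 11% may already include some non-adherers.* Possible, since 8.10.1 also speaks of dropping out of treatment and the source of the figure is not shown. Overlap would reduce the loss but, as step 4 shows, would not remove it at 20 or 30% total exclusion.
- *How the weights are built is detail for the statistical analysis plan.* Also fair, and the cost of the weights could be small. But the per-protocol exclusion and the power statement are both fixed in the protocol.
- *A reader might infer that 90% ought to cover both comparisons jointly, so that 84% is a second failure.* The protocol does not support that. It names two comparisons, splits the level between them and gives each its own interval. Nowhere does it require both to succeed. Power per comparison is a legitimate target for such a design.

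**Conclusion.** The point holds as a mismatch between two sections. The 90% in 11.1 is true per comparison for 73 effective children per arm. It is not true of the weighted per-protocol analysis of the planned 249 once non-adherence goes materially beyond the one-child slack, or once the weights cost any noticeable precision. At SD 1.7, and over the assumed range of 5 to 30% non-adherence, power is about 89 to 76% with costless weights and about 85 to 72% with a design effect of 1.1. These figures rest on assumed adherence and weighting, on an unchanged SD in the per-protocol set, and on dropout and non-adherence being separate losses.

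The significance level, the estimator and the decision rule are not affected, and any lost precision will show in the reported intervals. A reader might also infer that the trial must be enlarged. That does not follow: what is wrong is the power statement, and correcting it is enough.

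**What to change.** In section 11.1:

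1. State that 90% is the power per comparison and applies to 73 effective per-protocol children per arm.
2. Give the power of the planned 249 for the primary weighted per-protocol analysis over a range of adherence and weight design effect, as in the table above. Label both as assumptions and say whether the 11% includes any non-adherers.
3. Credit no precision gain from baseline covariates in this statement. Program is the only predictor in the primary model, and the covariates enter only through the weights.

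This costs a few sentences and a small table, and a less favourable power figure. No extra children are needed. It should be done before database lock.

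Two additions are optional. The joint power of about 84% at 73 per arm can be reported as clarification. Holm could replace the fixed split: if one comparison excludes the margin with its two-sided 97.5% interval, the other is judged with a two-sided 95% interval. That keeps the familywise one-sided error at 2.5% and raises joint power to about 90% at 73 per arm. The price is that the level of the second interval depends on the first result. Holm does not cure the per-protocol shortfall.

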## 11.2 Planned recruitment rate

The number of recruiting sites is 30, divided over the French-speaking and Dutch-speaking part of Belgium. Sample size per site differs and depends on number of the SLTs' active clinical hours in the treatment of stuttering and the diversity of the caseload (SLT treats only stuttering or also other disorders). We know most of the participating sites and know that nearly all ( $\geq 95\%$ ) of PCWS will be eligible for this trial.

We estimate, based on the survey that we sent to the sites that showed an interest to participate, that they will have maximum one PCWS per month eligible. We expect that about 2/3 will participate. Assuming that on average 1.5 PCWS per 3 months per site give consent (more specifically at least one of their parents), are eligible and willing to participate and assuming a recruitment period of 18 months, we will be able to include 249 participating PCWS.

## 11.3 Statistical analysis plan

### 11.3.1 Summary of baseline data and flow of patients

- Compare demographics like age, gender, comorbidities (Autism Spectrum Disorder, ADHD, language disorders...) and parent profile between the three programs. Means and standard deviation per group will be reported for age. For gender and comorbidities numbers and percentages are reported.
- Compare the stuttering state at baseline between the three programs using stuttering severity score (%SS) and the stuttering onset questionnaire. For the continuous variables means and standard deviations are reported (in case of skewness median and interquartile range are reported). For the categorical variable numbers and percentages are reported.
- Comparing the different questionnaires at baseline between the three programs (KiddyCat, EQ-5D-Y proxy 1, CBQ-short version, parent report about PCWS's stuttering severity and about their satisfaction of the PCWS's communication in everyday speaking situations). Means and standard deviations are reported (or median and interquartile range as appropriate). For the answers to the ISPP-questionnaire, frequencies and percentages are reported per program.

- A consort flow diagram will be produced to get an overview of the number of patients available at each stage: eligibility, randomisation, allocation, discontinuation and follow-up.

### 11.3.2 Primary outcome analysis

The %SS at 18 months post-randomisation will be determined in two video samples (at home and in the treatment session) and the average will be used.

Considering this is a non-inferiority trial, the primary endpoint is analysed in first instance in the per-protocol population. The per-protocol population are all eligible children who followed the treatment for at least 80%. To establish this, the SLT will carry out a compliance and fidelity checklist for each treatment session (Appendix 9). To correct for the fact that the per-protocol population is a subset of the randomised population we use a weighted linear regression model with %SS at 18 months post-randomisation as outcome and program as predictor and weighting individuals with inverse probability weighting. The weights which are determined in the full dataset of adherers and non-adherers are estimated as an individual's probability to adhere to a certain program given observed confounders like gender, age at assessment, comorbidities, family history of stuttering and recovery of stuttering, parent profile, baseline stuttering severity assessment (%SS and SR), and temperament (CBQ-short version). Post-hoc comparison of SCBT compared to LP and Mini-KIDS to LP using a two-sided 97.5% (correction for two comparisons) confidence interval for the difference in %SS will be compared to the non-inferiority margin.

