## **5 TRIAL DESIGN**

This study is a three arm, 1:1:1 randomised, open-label pragmatic comparative trial comparing Mini-KIDS, SCBT and the LP.

To show non-inferiority of Mini-KIDS compared to LP and SCBT compared to LP a parallel group design will be used. Stratified randomisation will be used according to site (30 sites) and gender.

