## 8.3 Trial randomisation

Stratified randomisation will be used according to site (30 sites) and gender. We will use a minimisation procedure to randomize. Minimisation assures similar distribution of selected participant factors between study groups. The first participant is truly randomly allocated; for each subsequent participant the imbalance score is computed based on all previous allocations as well as the hypothetical allocation of the current participant to each

treatment. The preferred treatment is then selected by choosing the treatment allocation associated with the smallest imbalance score.

The distance measure used to calculate the imbalance score is marginal balance. Marginal balance computes the cumulative difference between every possible pair of level counts (i.e. the number of participants in that particular factor level).

The allocation of the new participant is then made at random with a heavy weighting in favour of the intervention that would minimise imbalance. The remaining probability is equally divided between the non-preferred treatments. Full details will be provided in a separate document with restricted access.

If siblings or twins are eligible for this trial, only one child participate in the study otherwise there will be a dependency in the data. It is not feasible for a parent to implement two different treatment approaches. To avoid confusion, the second PCWS will receive the same treatment approach but will not be included in the study.

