### 11.3.3 Secondary outcome analysis

- Different sensitivity analysis will be done to evaluate the differences between the programs at 18 months post-randomisation. A linear regression model with %SS as outcome and type of program as a predictor will be considered with inclusion of other factors like gender, age at assessment, comorbidities, family history of stuttering and recovery of stuttering, baseline stuttering severity assessment (%SS and SR), and temperament (CBQ-short version). Linear regression assumptions will be checked and if needed transformations or other models will be explored. This analysis will be done in the per-protocol (naïve per-protocol) as well as in the intention-to-treat population. For the intention-to-treat population children who drop out from the study get the last recorded %SS carried forward.
- In the secondary analysis we will also consider the comparison between Mini-KIDS and SCBT.
- As %SS is measured repeatedly (3, 6, 9, 12, 18, 24, 60 months post-randomisation) we can consider a linear mixed model with child as random intercept to compare the evolution over time between the programs and to get an even more precise estimate of the difference at 18 months post-randomisation. The linear mixed model also allows the inclusion of confounders and also for this

model assumptions will be checked and if needed revised. This analysis will be done in the per-protocol as well as in the intention-to-treat population.

- SR (also averaged over home and treatment session sample), score on the KiddyCAT and EQ-5D-Y-proxy 1 at 18 months post-randomisation will be compared between the three programs using an analysis of variance and answers to the ISPP-questionnaire using a Chi-square test. These outcomes will also be studied in a multiple linear regression model (with confounders as mentioned before) with adjustment for their baseline values. The same analysis will be done for the EQ-5D-Y-proxy 1 scores at the long-term follow-up at 2 years and 5 years post-randomisation.

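### The primary regression has program as its only predictor: baseline %SS and gender enter only the adherence weights and site enters no model, so precision is given up

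*Protocol*

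**What the plan says.** Protocol section 8.3 sets the allocation: "Stratified randomisation will be used according to site (30 sites) and gender", and "We will use a minimisation procedure to randomize". Section 5 gives the ratio as 1:1:1.

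Section 11.3.2 then fixes the primary analysis in the per-protocol population: "we use a weighted linear regression model with %SS at 18 months post-randomisation as outcome and program as predictor". Each child is weighted by the inverse probability of adhering to the program. That probability is estimated "given observed confounders like gender, age at assessment, comorbidities, family history of stuttering and recovery of stuttering, parent profile", and the list goes on to "baseline stuttering severity assessment (%SS and SR), and temperament (CBQ-short version". A two-sided 97.5% interval from this regression is compared with the margin. So gender and baseline severity appear in the weight model and not in the outcome model. Site appears in neither.

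Section 11.3.3 plans a covariate-adjusted regression, "with inclusion of other factors like gender, age at assessment, comorbidities", whose list also reaches baseline %SS, but only as a sensitivity analysis. Its list does not name site either. The mixed model in the same section has child as its only random effect.

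Section 11.1 sizes the trial: "The non-inferiority margin was set at 1.0% SS", SD 1.7 for %SS at 18 months, one-sided 1.25% per comparison, 90% power and no true difference. This gives 73 per arm, and 249 randomised after 11% dropout.

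**The concern.** The protocol states this model outright, so it is a choice that can be reviewed and not a detail left to the SAP. The choice gives up precision that is free.

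Baseline %SS is scored by the same blinded analysts and the same method as the outcome. Section 8.7.1 has the baseline videos uploaded before the arm is revealed, so it is a clean pre-treatment covariate. Site and gender were chosen for balance at allocation. If such factors predict the outcome and the model leaves them out, the standard error is too large for the balance actually achieved.

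The plan is also uneven. In section 11.3.3 the regressions for SR, KiddyCAT and EQ-5D-Y adjust for the baseline value of each outcome, and a mixed model is proposed partly to sharpen the 18-month estimate. The analysis that decides non-inferiority has neither benefit. What is at stake is a wider interval than necessary, and so a somewhat higher chance of an inconclusive result when a program really is non-inferior.

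**Working it through.** **Inputs from the protocol.** Section 11.1: margin 1.0 %SS, SD 1.7, one-sided alpha 0.0125, power 0.90, true difference 0, dropout 11%. Section 8.3: 30 sites. Not given: the correlation r between baseline and 18-month %SS, and the site intraclass correlation (ICC). Both are treated as ranges below.

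**Step 1. The plan's own figure.** By the normal approximation, n per arm = 2 × 1.7² × (2.241 + 1.282)² / 1.0² = 71.7, so 72. The noncentral t calculation gives exactly 73 (power 90.0%; 89.6% at 72). Inflating, 73 / 0.89 = 82.02, so 83 per arm, and 3 × 83 = 249. The stated numbers reproduce, and they use the raw outcome SD. The sample size therefore matches an unadjusted model.

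**Step 2. Effect of adding baseline %SS.** The residual SD is 1.7 × √(1 − r²). The standard error of a difference is that SD × √(2/73). The 97.5% half-width is 2.241 × SE (normal quantile). Power is from the noncentral t with 144 degrees of freedom and noncentrality 1.0/SE. For r = 0, SE = 1.7 × √(2/73) = 0.281, so the half-width is 0.631.

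| r (assumed) | residual SD | half-width, %SS | narrower by | power |
|---|---|---|---|---|
| 0 | 1.700 | 0.631 | 0% | 90.0% |
| 0.1 | 1.691 | 0.628 | 0.5% | 90.3% |
| 0.2 | 1.666 | 0.618 | 2% | 91.2% |
| 0.3 | 1.622 | 0.602 | 5% | 92.7% |
| 0.4 | 1.558 | 0.578 | 8% | 94.5% |
| 0.5 | 1.472 | 0.546 | 13% | 96.6% |

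**Step 3. Do the weights already deliver this?** In a simulation, 249 children at 30 sites were balanced across arms, and adherence weights were estimated from baseline, gender and arm (600 runs per scenario). It compared the weighted program-only model with weighted models that add covariates. The entries are mean standard errors.

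| r, ICC (assumed) | program only | + baseline, gender | + baseline, gender, site terms |
|---|---|---|---|
| 0, 0 | 0.293 | 0.294 | 0.302 |
| 0.3, 0.05 | 0.294 | 0.280 | 0.281 |
| 0.5, 0.05 | 0.295 | 0.255 | 0.253 |
| 0.5, 0 | 0.295 | 0.255 | 0.262 |

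Adding baseline and gender cuts the standard error by 5% at r = 0.3 and 14% at r = 0.5, although both were already in the weights. The weights do not replace outcome covariates. At r = 0 there is nothing to gain.

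**Step 4. Site.** There are 249/30 = 8.3 children per site. Entering 29 fixed site terms gained almost nothing at ICC 0.05 and cost a little at ICC 0. A rough formula, √(1 − ICC) with the t quantile adjusted for the lost degrees of freedom, narrows the interval by about 2%, 5% and 10% at ICC 0.05, 0.10 and 0.20. The simulation shows that even the 2% is optimistic. This favours a random intercept over fixed terms.

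**The case against.** The strongest defence is that nothing here is wrong. The trial was sized on the unadjusted SD and analysed without adjustment, so the two agree, and at 73 evaluable per arm the planned 90% power is met. Leaving out balancing factors tends to make the interval conservative, so it does not create a false claim of non-inferiority. All of this stands.

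A reader might infer that the primary analysis ignores baseline %SS and gender altogether. It does not, because both are in the weight model of section 11.3.2. A reader might also infer that the weights do nothing about differences between arms. That is too strong. In a separate simulation with an assumed 80% adherence that depended on baseline differently by arm, the mean baseline difference between two per-protocol arms was 0.32 SD unweighted and 0.00 SD weighted. What the weights leave is chance imbalance and outcome variance.

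The gain may also be small. Section 2 expects near-zero stuttering in all three arms at 18 months, and such a floor could make r low. The protocol therefore does not support calling baseline %SS the main source of precision.

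It is tempting to quote a larger gain for a smaller per-protocol group, for example 59 per arm. The protocol gives no share of children expected to adhere. Its 80% is a threshold for each child, so such a figure would be pure assumption.

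Finally, section 11.3.3 will produce adjusted estimates in both populations. They are secondary, so they do not change the interval that is compared with the margin.

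**Conclusion.** The point holds as a matter of efficiency. The primary outcome model has no covariate besides program, the weights do not recover the lost precision, and site is used in allocation but named in no model in section 11.3. On the protocol's own inputs with 73 evaluable per arm, the benefit of adjusting for baseline runs from nothing at r = 0 to 6.6 percentage points of power at r = 0.5 (96.6 − 90.0). It is about one point at r = 0.2 (91.2 − 90.0). These figures assume a linear baseline relation, a common SD of 1.7 and no true difference, and r itself is unknown. Any gain from site is probably small.

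The documents do not support reading this as an invalid interval, an error in the sample size, or a route that leads directly to failure. It is a worthwhile improvement that costs almost nothing, and the trial's validity does not depend on it.

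**What to change.** Amend section 11.3.2, and carry the same wording into the SAP before database lock:

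- Primary model: %SS at 18 months on program, baseline %SS (average of the home and session samples) and gender, with site as a random intercept. Keep the adherence weights.
- Intention-to-treat model: the same covariates.
- Sensitivity analysis: the weighted program-only model as now written.

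The method for standard errors with estimated weights can be settled in the SAP. The sample size need not change, because any gain is extra margin over the planned power. The cost is wording only: baseline %SS, gender and site are already recorded for the trial.

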- For the continuous measures SR, EQ-5D-Y proxy 1, measured at different time points we can compare the evolution over time between the programs using a linear mixed model. This model also allows to look at differences at a specific time point in a post-hoc comparison. For the answers to the ISPP-questionnaire measured at different time points this can be done using a generalized linear mixed model. For the ordinal outcomes parent report about their PCWS's stuttering severity and their satisfaction about the PCWS's communication in everyday speaking situations depending on variability a linear mixed or generalized linear mixed model will be used.
- The number of weeks, the number of treatment sessions, the treatment time needed until the maintenance phase begins will be compared between the three programs using an ANOVA or Kruskal Wallis test as appropriate. This outcome will also be studied in a multiple linear regression model adjusting for possible confounders.
- We will look at the proportion of children that are successful (defined as  $<1\%$  SS and  $SR \leq 1$ ) at 18 months and at 5 years post-randomisation. They will be compared by a Chi-square test (or Fisher's exact test as appropriate) between the three programs. The time to reach success between the three programs will be compared with a Kaplan-Meier plot and analyzed using a Cox regression model with correction for confounders.
- %SS and SR at 18 months post-randomisation will be evaluated separately for the videos at home and for the videos recorded during the treatment sessions using linear regression models as described for the averages of the two samples.
- For the above analysis we will first consider the intention-to-treat population to preserve randomization, if necessary also per-protocol population will be considered.
- Safety analysis will be done in all patients that are randomised.
- Numbers of children who drop out and reasons for drop out, as well as leave the allocated treatment arm (numbers, reason and switched treatment) will be described per treatment. Numbers per program will be compared using a Chi-square test (or Fisher's exact test as appropriate). A time to drop-out analysis or a time to switch analysis will be performed in case  $> 10\%$  drop-out or a 10% switch was present in the trial.

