#### *11.3.4 Procedure(s) to account for missing or spurious data*

Most of the data is routinely collected as standard of care and the SLT will be in contact with the PCWS regularly to ensure collection of all relevant data.

The SLT follows up on the missing data and records any reasons for missing data in PCWS' speech-language therapy files and the eCRF (REDCap).

For the sensitivity analysis of the primary outcome, we considered last observation carried forward, as an alternative we will also explore multiple imputation techniques and compare results.

The proposed linear mixed model allows that subjects have missing values at certain time points as the model uses all available data points per subject. The missing value assumption of the model is Missing At Random which means that missing values can only be dependent on the observed responses which seems a reasonable assumption in this case.

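### The primary per-protocol model weights for adherence only, so it is complete-case for any adherent child without an 18-month %SS; how many such children there will be depends on a counting rule that 11.3.2 does not give

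*Protocol*

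**What the plan says.** **Primary model.** Protocol 11.3.2 analyses 18-month %SS first in the per-protocol population, by a linear regression with inverse probability weights. On the weights: "The weights which are determined in the full dataset of adherers and non-adherers are estimated as an individual's probability to adhere". The listed predictors are baseline characteristics such as gender, age, comorbidities, family history, parent profile, baseline severity and temperament.

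**Missing data.** Section 11.3.4 says: "For the sensitivity analysis of the primary outcome, we considered last observation carried forward, as an alternative we will also explore multiple imputation techniques". It then relies on missing at random for the linear mixed model. Section 11.3.3 carries the last %SS forward for study dropouts in the intention-to-treat regression. It lists the mixed model among the secondary analyses, in both the per-protocol and intention-to-treat populations.

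**Planned loss.** Section 11.1: "Taking into account a 11% dropout", which takes 73 children per arm to 83 and gives 249 in total.

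**Adherence.** Section 11.3.2 bases the 80% on compliance and fidelity checklists completed for each session. Sections 8.9.1 and 8.9.2 apply 80% to the treatment aspects present. Section 8.9 also counts attendance and length of treatment under dosage. None of these says how a child who leaves early is scored.

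**Follow-up.** Section 8.10.1 keeps children who stop treatment in data collection unless consent is withdrawn.

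**The concern.** A child contributes to the primary regression only if two conditions hold: the child is classed as adherent, and an 18-month %SS exists. The weights address the first condition only. Take a family that withdraws consent or is lost at month 9 with good checklists up to then. If the 80% is judged on the sessions held, that child is an adherer. The child then drops out of the regression and no weight stands in for the missing value.

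Such loss may be related to response. Families of children who do not improve may leave, and families of early finishers may not come back for a recording. The adherence weights use baseline data only, so they cannot correct loss that depends on how the child was doing at months 3 to 12. If poor responders are lost more often from Mini-KIDS or SCBT than from LP, the observed difference shrinks and a program that is truly worse by the margin is declared non-inferior too often. The opposite pattern would push the other way.

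**Working it through.** **Inputs from section 11.1.** Margin: "The non-inferiority margin was set at 1.0% SS". SD: "we estimated a value of 1.7 for the standard deviation at 18 months on %SS". True difference 0. Design: "using a power of 90% and a one-sided significance level of 1.25% we need 73 children in each group". Dropout 11%.

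**The plan's own figure.** n per arm = 2 × 1.7² × (2.241 + 1.282)² / 1.0² = 71.7, so 72 by the normal approximation. At 73 per arm a noncentral-t calculation gives power 0.89996. Inflation: 73 / 0.89 = 82.02, so 83 per arm and 3 × 83 = 249. The stated figures are reproduced.

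**Power.** 83 × 0.89 = 73.9 per arm, power 0.904. The expected loss of numbers is already paid for. What remains is possible bias.

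**How many children have no rule.** 11% of 249 = 27.4 (9.1 per arm). If a share s of them counts as adherent, the number is 27.4 × s:

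| s | children in total |
|---|---|
| 0% | 0 |
| 25% | 6.8 |
| 50% | 13.7 |
| 75% | 20.5 |
| 100% | 27.4 |

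The protocol does not give s.

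**Bias.** Let p be the proportion of an arm that is adherent but lost, and D the amount by which lost children's %SS exceeds that of observed children. The observed arm mean is too low by p × D. The contrast (experimental minus LP) is therefore too low by p_E × D_E − p_LP × D_LP. This is zero when the two products are equal.

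**Error at the margin.** SE = 1.7 × √(2/73) = 0.281. One-sided error at a true difference of 1.0 = Φ(−2.241 + bias / 0.281).

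Assumptions, not in the protocol: loss of 17% in an experimental arm and 5% in LP (average 11%), and D of 1 to 2 %SS in both arms.

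| Lost children who are adherent | D | Bias | Error |
|---|---|---|---|
| all | 1 | (0.17 − 0.05) × 1 = 0.12 | 3.5% |
| all | 2 | (0.17 − 0.05) × 2 = 0.24 | about 8% |
| half | 1 | 0.06 | 2.1% |
| half | 2 | 0.12 | 3.5% |
| equal, similarly related loss | any | 0 | 1.25% |

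The half rows take all randomised children as the denominator. With adherers as the denominator, and no other non-adherers, the lost shares are 0.085 / 0.915 = 0.093 and 0.025 / 0.975 = 0.026. The bias is then 0.07 to 0.13, which changes little.

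**Equal loss, unequal relation to response.** If 11% is lost in each arm, all adherent, and only one experimental arm's lost children are worse, the shift is 0.11 × D. That is 0.11 (error about 3.2%) for D = 1 and 0.22 (about 7.1%) for D = 2.

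**The case against.** **It is a matter for the SAP.** Section 11 leaves details to a separate plan that is not shown, and a missing-outcome rule could be called a detail. This would settle the matter if the protocol were silent. It is not: it specifies what the primary weights model and states which analyses each missing-data method serves. An SAP that follows 11.3.2 and 11.3.4 inherits the gap.

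**The 11% overstates the problem.** A reader might infer that all the planned dropouts leave the primary analysis uncorrected. The protocol does not support that. A dropout classed as non-adherent is represented through the adherence weights, given the baseline covariates. Whether a child lost at month 9 is adherent cannot be read from the text: the 80% of treatment aspects points to a checklist count, while attendance and treatment length under dosage point the other way. So 27 is an upper bound.

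**Safeguards exist.** Children who stop treatment stay in follow-up. Section 8.10.3 requires three contact attempts. The per-protocol mixed model uses all visits under missing at random. The intention-to-treat analyses use carried-forward and imputed values. Dropout is compared by arm. These reduce the number of missing values and would help to expose a problem. None changes the primary estimate, and the mixed model is a secondary analysis described without adherence weights.

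**The size is constructed.** The arm-specific loss and the 1 to 2 %SS gap are assumptions, and the two suggested reasons for loss can offset each other within an arm. This stands: the figures show sensitivity and predict nothing.

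**Conclusion.** The point holds in a limited form. Followed as written, the primary non-inferiority analysis corrects for non-adherence and not for a missing 18-month %SS among adherers. It affects between 0 and about 27 of 249 children, depending on an adherence count that 11.3.2 leaves open. If all lost children are adherent, loss is 17% against 5%, and lost children are 1 to 2 %SS worse, the bias is 0.12 to 0.24 %SS towards non-inferiority and the one-sided error is about 3.5% to 8%. With half of them adherent it is about 0.06 to 0.12 %SS and 2.1% to 3.5%. With equal, similarly related loss there is no bias.

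Two stronger conclusions do not follow. The trial is not underpowered for dropout, since 83 per arm allows for it. Nor is the primary result shown to be biased, since the protocol gives no loss or response pattern by arm. The point merits a change because the decision rests on this one estimate and the data for a better method are already collected.

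**What to change.** In section 11.3.2:

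1. State whether a child lost or withdrawn before 18 months counts as adherent, and how the 80% is computed for that child.
2. Make multiple imputation of the 18-month %SS part of the primary weighted analysis. Impute within arm, from the baseline covariates and the available month 3 to 12 %SS. Keep the complete-case version as a sensitivity analysis, and align 11.3.4 with this.
3. If an observation weight is preferred to imputation, keep its model small, for example arm, baseline %SS and last %SS, pooled across arms. At 11% loss there are at most about 9 missing outcomes per arm, so a within-arm model with the nine or so covariates of 11.3.2 would have about one event per covariate or fewer.

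The 18-month success proportion in 11.3.3 is a subsidiary matter and could be derived from imputed %SS and SR.

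The cost is some extra analysis work and reliance on missing at random given the month 3 to 12 values. No new data are needed and the sample size of 249 is unchanged. The rule should be fixed before outcome data are seen.
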